**Patient interviews:**

For the interviews, up to 103 men who get circumcised and consent will be randomly selected to have a private *face-to-face interview* at three points in time: prior to their procedure, 14 days and 90 days after procedure. Interviewer administered questionnaires will be used to collect required data.

**Healthcare worker interviews:**

Among healthcare workers, all healthcare providers involved in this PrePex study will given the opportunity to complete interviews on their opinions and views on the PrePex™ device. All healthcare workers will be consented (Appendix 2); participation is voluntary. These interviews will enable us to evaluate the acceptability of the PrePex™ procedure from service providers. Interviews will take place approximately 4 weeks after study implementation begins.

**Table 1: Study timeline**

| **Table 1: Protocol Description and Timing of Assessments** | | | | | | | | |
| --- | --- | --- | --- | --- | --- | --- | --- | --- |
|  | **Screening and Recruitment Visit** | **Application Visit** | **Removal Visit** | **Physical Examination of the genital Visit** | **Physical Examination of the genital Visit** | **Physical Examination of the genital Visit** | **Physical Examination of the genital Visit** | **Physical Examination of the genital Visit** |
| **Visit #** | **1** | **2** | **4** | **5** | **6** | **7** | **8** | **9, 10, 11, 12, 13** |
| **Day (D)/week (w)** | **–7 to D0** | **D0** | **D7** | **D9** | **D14** | **D21** | **D28** | **D35, 42, 49, 56, 63** |
| Informed consent | X |  |  |  |  |  |  |  |
| Screen with Inclusion/exclusion criteria | X |  |  |  |  |  |  |  |
| Participant specimen collection for CD4 count | X |  |  |  |  |  |  |  |
| Medical history & Demography | X |  |  |  |  |  |  |  |
| Current medication including pain killers | X | X | X | X | X | X | X | X |
| Psychosocial interview |  | X |  |  | X |  |  | X (D90) |
| Genital examination and potential pictures | X | X | X | X | X | X | X | X |
| Video procedure |  | X | X |  |  |  |  |  |
| Device application |  | X |  |  |  |  |  |  |
| Foreskin removal |  |  | X |  |  |  |  |  |
| Device removal |  |  | X |  |  |  |  |  |
| Subject's subjective pain, tingling and discomfort evaluation (VAS score) |  | X | X | X | X | X | X | X |
| Evaluate side effects and AE |  | X | X | X | X | X | X | X |
| Statistical analysis of data |  |  |  |  |  |  |  | Interim safety report |

2. Would subjects undergo these or similar procedures (medical, psychological, educational, etc.) if they were not taking part in this research?  No  Yes If “Yes,” describe how the study procedures differ from what subjects would otherwise undergo.

HIV+ men are not excluded from VMMC according to the Zimbabwe MOHCC, but the program is intended as an HIV prevention program and focuses on HIV-negative men. The PrePex™ device was approved by the Zimbabwe MOHCC for use among HIV-negative men ages 18 and older, and routine implementation began in early 2014. This protocol follows the standard protocols for this activity, extending the target group to include HIV-positive men. Men participating in this study are currently eligible for forceps-guided MC. As with all MOHCC VMMC program services, participants in the study will also receive VMMC at no cost.

3. Check all of the boxes below that apply to your research:

**Drug administration**

Administration of a drug (either FDA-approved or investigational) for research purposes to a subject-patient during general or regional anesthesia.

Administration of a drug (either FDA-approved or investigational) for research purposes to a subject-patient during the 1.5 hours preceding general or regional anesthesia.

**Blood lines**

Inserting an intravenous (central or peripheral) or intra-arterial line for research purposes in a subject-patient **during** general or regional anesthesia.

**Sample collection**

Obtaining samples of blood, urine, or cerebrospinal fluid for research purposes while a subject-patient is under general or regional anesthesia.

Obtaining a research sample from tissue or organs that would not otherwise be removed during surgery, while the subject-patient is under general or regional anesthesia.

**Radio-isotopes**

Administration of a radio-isotope for research purposes during the 3 hours prior to anesthesia or while a subject-patient is under general or regional anesthesia.

If you checked this box, you are responsible for informing **in advance** all appropriate clinical personnel (e.g., nurses, technicians, anesthesiologists, surgeons) about the administration and use of the radio-isotope, to ensure that any personal safety issues (e.g., pregnancy) can be appropriately addressed. This is a condition of IRB approval.

**Experimental devices**

Implantation of an experimental device while a subject-patient is under general or regional anesthesia.

**Other experimental manipulations or procedures**

Other manipulations or procedures performed solely for research purposes while a subject-patient is under general or regional anesthesia (e.g., experimental liver dialysis, experimental brain stimulation)

**None of the above**

None of the above apply to my research

4. If you checked any box in question #3 except “none of the above”, answer the following questions:

a. Provide the name and institutional affiliation of the physician anesthesiologist who is a member of your research team or who will serve as a safety consultant about the interactions between your research procedures and the general or regional anesthesia of the subject-patients. If your procedures will be performed at a UW Medicine facility or affiliate, the anesthesiologist must be a UW faculty member.

Not applicable

b. If you have not yet consulted with an appropriately qualified person about this issue, describe in detail your plans to do so. The IRB will not approve your application without this consultation. If UW Department of Anesthesiology approval has been obtained, please provide the Department’s letter of support.

Not applicable

**C. DECEPTION**: If any deception or withholding of complete information is required for this activity, explain why this is necessary and attach a protocol explaining if, how, when, and by whom subjects will be debriefed.

There is no deception or withholding of completed information required of this activity.

**D. SUBJECTS**

The IRB reviews the number of subjects you plan to study in the context of risks and benefits. If your research is approved for a specific number of subjects, the data from any “extra” subjects cannot be described as having been obtained with IRB approval.

See the HSD website for the definition of “human subject” <http://www.washington.edu/research/hsd/docs/1253>. Before answering the questions below, be sure that you are familiar with the definition.

1. **Subject groups/categories and numbers.** Complete this table by listing:

- Your groups or categories of subjects. “Group” should be defined as appropriate for your research.
  - “Units” within a group. For most research, a group will consist of individuals, such as children aged 8-12, or individuals with high blood pressure. However, this will not be true for all research. Examples of groups with “units” that are not individuals:
    - Dyads such as Alzheimer’s-patient-and-caregiver, with one group of the dyads assigned to one intervention (e.g., behavioral modification) and another group of the dyads assigned to a comparison intervention(e.g., drug treatment).
    - Families. For example, a study of mental health interventions for homeless families might have one group of 30 families assigned to one intervention and another group of 30 families assigned to a different intervention.
    - Other. For example, the “units” in autism research might be an autistic individual and all his/her living blood relatives. The units in an academic excellence study might be a student-parents-teacher unit.
  - Types of groups. There are many ways in which subjects might be grouped. Examples:
    - By intervention. Example: research comparing two different drugs for high blood pressure.
    - By subject population. Example: research comparing the incidence of domestic violence in families living in urban settings versus families living in rural settings.
    - If you have only one group, fill in only one line in the table. Add more lines if needed.
- The age range of each group.
- The upper limit/number of **completed** subjects you need for each group. ***Completed*** *means that all research procedures involving the subjects or the obtaining of specimens/records/data have been completed as far as is possible for each subject, including any follow-up (such as follow-up access to medical records.) In some cases, such as an online survey, it is not possible to predict the number of subjects who will complete the research. If you cannot predict or describe the maximum number of subjects you need in each group, check the appropriate box and provide your rationale in the space provided below the table.*

| **Group name/description for routine program activities** | **Age range of subjects** | **Maximum desired number of individuals (or other group unit, such as families) who will complete the research.*** | **Cannot provide a number.**** |
| --- | --- | --- | --- |
| HIV-positive VMMC clients (males) | 18+ years | 400 |  |
| Healthcare providers | 18+ years | Up to 20 | ****** |
|  |  |  | ****** |
|  |  |  | ****** |

***This is the number of subjects (individuals, dyads, families, etc., as appropriate) in each group that will be considered for approval by the IRB.**

****If you cannot predict or describe the maximum number of subjects you need in each group:**

Provide your rationale and description of research scope here. *Include any information or estimates you might have about the number of subjects, so that the IRB has a sense of the scope of your research. For example, your research might be a small pilot study of all patients presenting with a rare disease at UW Medicine in the next year. Or, it might involve a survey posted on Craig’s List for two weeks that could result in thousands of responses.*

| **NOTE: In your annual Status Report, you will be asked to complete the table below with your subject numbers. While developing your research protocol, please plan ahead so that you will have an accurate record of the subject numbers above.**  **This is for illustration only. Do not complete this table.**   \|  \| # Completions \| \| \| \| # Ongoing (subjects still involved) \| # Withdrawals, drops, lost \| \| \| \| --- \| --- \| --- \| --- \| --- \| --- \| --- \| --- \| --- \| \| Group Name / Description \| Total approved by IRB \| A At time of last Status Report \| B Since last Status Report \| A + B Total to date \| C At time of last Status Report \| D Since last Status Report \| C + D Total to date \| \|  \|  \|  \|  \|  \|  \|  \|  \|  \| \| DO NOT COMPLETE \|  \|  \|  \|  \|  \|  \|  \|  \| \|  \|  \|  \|  \|  \|  \|  \|  \|  \| \|  \|  \|  \|  \|  \|  \|  \|  \|  \| |
| --- | --- | --- | --- | --- | --- | --- | --- | --- | --- | --- | --- | --- | --- | --- | --- | --- | --- | --- | --- | --- | --- | --- | --- | --- | --- | --- | --- | --- | --- | --- | --- | --- | --- | --- | --- | --- | --- | --- | --- | --- | --- | --- | --- | --- | --- | --- | --- | --- | --- | --- | --- | --- | --- |

2. Explain how you will achieve equitable subject representation in the following categories. If not applicable, justify exclusions.

The Zimbabwe MOHCW has determined the eligibility criteria for VMMC. I-TECH operates as an implementer of their national program. Those criteria are:

a. Age (minors, elderly): N/A: The VMMC program using PrePex™ is open to all men ages 18+, with a specific target for HIV- sexually active men, ages 18-29. Men in this study will be recruited if they are HIV-positive and meet all other study eligibility requirements.

b. Gender: The VMMC procedure is only available for men

c. Ethnic and racial minority populations: We anticipate the ethnic and racial distribution of the study population will reflect the ethnic and racial distribution of men willing to participate in the VMMC program in the areas in Zimbabwe we are working in.

3. What characteristics (inclusion criteria) must subjects have to be in this study? (Answer for each subject group, if different.)

Inclusion Criteria:

- Agrees to take an HIV test
- HIV sero-positive
- WHO HIV clinical stage 1 or 2
- Age 18 years and above
- Agrees to be circumcised by PrePex™
- Able to understand the study procedures and requirements
- Completes VMMC counseling
- Agrees to return to the health care facility for follow-up visits (or as instructed) after his circumcision until complete healing 7 weeks from device application (Day 49 visit) or until cleared by a clinician, whichever is later
- Able to comprehend and freely give informed consent for participation in this study

4. What characteristics (exclusion criteria) would exclude subjects who are otherwise eligible from this study? (Answer for each subject group, if different.)

Exclusion Criteria:

- Known bleeding/coagulation abnormality (excessive bleeding from nosebleeds, pulled tooth, or gums)
- Uncontrolled diabetes (frequent treatment in a clinic or recent hospitalization for diabetes, frequent infections, hypertension, or kidney disease),
- Active genital infection, anatomic abnormality or any other condition, which in the opinion of the investigator prevents the subject from undergoing circumcision using PrePex.
- HIV sero-negative
- HIV status unknown
- WHO HIV stage 3 and above
- Latex allergy
- Does not agree to PrePex

5. Describe the subject recruitment strategies you will use for each group of subjects. (Attach advertisements, flyers, contact letters, telephone contact protocols, Health Sciences recruitment web site template, etc.)

Study staff may identify potential participants from any of the following sites: OI and VCT centres, Zengeza clinic, Chitungwiza hospital, and OI clinics at Beatrice and Wilkins hospitals. After learning about the study, those who agree to be circumcised using PrePex will be requested to visit Zengeza clinic for further screening by the study coordinator using eligibility criteria before actual recruitment into the study. Services at the study site, Zengeza clinic, will be offered every day from 8:00 am to 4:00 pm except on Sunday.

6. Explain who will approach subjects to take part in the study and how this will be done to protect subjects’ privacy. (Attach letters of cooperation from agencies, institutions or others involved in subject recruitment.)

Participants will be recruited from any of the following sites: Voluntary testing and counseling (VCT) centers at Zengeza clinic and Chitungwiza hospital and opportunistic infection clinics (for HIV-positive patients) at Beatrice and Wilkins hospitals.

Trained counsellors at selected OI clinics or VCT centres will help identify potential participants by asking all men presenting to these sites if they would be willing to be contacted by a study coordinator to set an appointment for PrePex MC screening. Men seeking care at OI clinic (existing HIV-positives) and men who test positive at these sites (new HIV-positives) after undergoing HTC according to Ministry of Health (MOHCC) guidelines (including pre- and post-test counseling) may be recruited. For men who are not confirmed in HIV-related care or do not have a confirmed, recent (within 4 weeks) HIV+ test result from a facility or testing station, they will undergo an HIV test using the Ministry of Health and Child Care (MoHCC) guidelines that include pre- and post-test counseling to confirm their HIV status as an eligibility criterion. Consent for HIV testing will be done according to MoHCC guidelines. Men aged 18 years or older, who are eligible for circumcision using the PrePex^TM^ device, and meet the inclusion criteria, will be included in the study. All eligible men will be invited to participate until the required sample size is achieved. Participants will be asked to provide their phone numbers and their written consent to be contacted over the phone and to be followed-up by home visit.

7. Explain what steps you will take during the recruitment process to minimize potential coercion or the appearance of coercion.

ZiCHIRe will train community mobilizers and health care workers on the ethics and principles of preventing coercion and maintaining confidentiality. Potential HIV+ VMMC clients will be informed that the procedure is voluntary, and they will be required to sign a consent/assent form to participate. Potential clients will also be informed they can withdraw from participation at any time for any reason, without penalty or prejudice, and will be informed that declining to participate in this study will not jeopardize their access to routine health are or VMMC services in Zimbabwe.

8. Will you give subjects gifts, payments, services without charge, or extra course credit?  No  Yes If yes, explain:

Participants will be compensated for their time and effort in this study. They will receive approximately US$6 per visit to take care of transport reimbursement, refreshment and client's time. Healthcare workers will receive $10 at time of interview. The reimbursement amounts are a requirement by Medical Research Council of Zimbabwe and were provided for participants in previous PrePex™ trials, including the ongoing trial for adolescents led by the same Zimbabwe PI.

9. Will any of the subjects or their third-party payers be charged for any study procedures?  No  Yes If yes, explain:

10. **Locations and research sites.** Provide the following information in list or table format for all locations at which any research procedures will occur. Be sure to consider: screening, recruiting, consenting, observation, intervention, data collection, data analysis, specimen analysis, and location of any consultants and collaborators. Recruiting script (Appendix 10) and flyer (Appendix 16) are attached.

- Geographical location and/or address
- Name of organization, agency, group, site, institution
- What procedures will occur at each location (how the location is involved in the research)
- Whether subject contact or interaction will occur at each site
- Whether consenting of subjects will occur at each site
- Whether each site, or individuals at the site, will obtain, use, or have access to coded or individually identifiable private information about subjects for research purposes

| **Site** | **Recruitment** | **Screening/Consent** | **PrePex Procedure** | **Follow-up/AE Response** | **Data Storage** | **Data analysis** |
| --- | --- | --- | --- | --- | --- | --- |
| Chitungwiza Hospital | X | X | X | X | X |  |
| Zengeza clinic in Chitungwiza | X | X | X | X | X |  |
| OI clinic at Beatrice Hospital | X |  |  |  |  |  |
| OI clinic at Wilkins Hospital | X |  |  |  |  |  |
| Zichire office, Harare, Zimbabwe |  |  |  |  | X | X |
| I-TECH/Seattle |  |  |  |  | X | X |

The PrePex™ device procedure will be performed by nurses/doctors at Chitungwiza Hospital and/or Zengeza clinic in Chitungwiza, outside of Harare Zimbabwe. Chitungwiza Hospital will be set up as a new training centre to increase the country capacity to train trainers of PrePex™ operators and assistants. Sites will have a PIMA machine so that clients can have their CD4 tested on site with immediate results. All study activities will take place at these sites from consent, procedure, interviews and all follow-up visits.. Sites will house all data and study-related information that includes names. Data management and confidentiality procedures are in place. Recruitment activities will take place at OI and VCT centers near the city of Chitinguwiza, including Zengeza clinic, Chitungwiza hospital and OI clinics at Beatrice and Wilkins hospitals. Analysis will take place at the Zichire office in Harare and in I-TECH/Seattle.

**Data Collection**

Overview table:

| Study Objective | Sample Size Est. | Sampling method | Data collection Methods | Tools |
| --- | --- | --- | --- | --- |
| 1.1.1 (Safety) | 400 | Purposive | Interview | CRF |
| 1.2.1 (Level of care) | 400 | Purposive | Interview  Observation | CRF |
| 1.2.2 (Acceptability) |  |  |  |  |
| Clients | 103 | Random | Interview | QES |
| Providers | All | Purposive | Interview | QES |
| 1.2.3 (Facilitators/Barriers) |  |  |  |  |
| Clients | 103 | Random | Interview | QES |
| Providers | All | Purposive | Interview | QES |
| 1.2.4 (Compliance with instructions) | 103 | Purposive | Interview | QES |
| 1.2.5 (AE monitoring) | 400 | Purposive | Interview  Observation | CRF |

If you are the direct recipient of federal funding for this project and other organizations are “engaged” in the research (see the Worksheet on Engagement), you are responsible for obtaining IRB approval from the other organizations or for requesting that the UW conduct the IRB review on behalf of that organization. See the document [SOP Research Collaborations or Multiple Performance Sites](http://www.washington.edu/research/hsd/docs/1644) and [WORKSHEET IRB Review Options](http://www.washington.edu/research/hsd/docs/1645) for more information.

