**The Primary Objectives are**:

- 1. To assess the safety of the PrePex™ device when applied to HIV positive men by assessing the rate of the clinical adverse events.

1. **The Secondary Objectives are:**
   1. To assess the level of care required to provide PrePex™ MC to HIV positive men, when taking into account the following parameters:
      1. PrePex™ procedure duration (a combination of the application and removal procedure times)
      2. Pain management at different stages of the procedure
      3. Time to complete healing, defined as, intact epithelium (unbroken skin) covering the epithelial as judged by the provider on visual inspection, meaning that none of the following are present: sutures, scabbing, drainage, moisture, gaps between epithelial edges or ulceration.]
   2. To evaluate the acceptability of the PrePex™ procedure to HIV-positive men as well as service providers.
   3. To evaluate Facilitators/Barriers for seeking VMMC among HIV-infected men
   4. To assess compliance with instructions to refrain from sexual intercourse until seven weeks post-placement-- Day 49 post-placement visit (6 weeks post-removal) or as instructed by a clinician, whichever is later, as a public health safety issue.
   5. Assess AE monitoring and reporting systems with respect to completeness and timeliness of reporting

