**B. RESEARCH PROCEDURES INVOLVED.**

1. Provide a complete description of: a. the study design, and b. sequence and timing of all study procedures that will be performed, e.g., volume of blood, size of biopsy, drug administration, questionnaire, name of psychological test. Provide this information for each phase of the study (pilot, screening, intervention and follow-up). **Use lay language**. Attach study flow sheet, if available.

- - 1. **Study Design**

This is a one arm, open label, prospective cohort study to assess the safety and acceptability of PrePex™ device circumcision when performed by trained PrePex™ MC Providers in a HIV infected male population. The study will involve 400 HIV+ men. The estimated study timeline of 18 months is:

| **Month** | **1** | **2** | **3** | **4** | **5** | **6** | **7** | **8** | **9** | **10** | **11** | **12** | **13** | **14** | **15** | **16** | **17** | **18** |
| --- | --- | --- | --- | --- | --- | --- | --- | --- | --- | --- | --- | --- | --- | --- | --- | --- | --- | --- |
| **Study Phase** | **Start-up** | | | **Recruitment** | | | | | | **Patient Follow-Up** | | | **Analysis and Report Writing** | | | | | |

The study will have two study components which will be concurrently implemented in an estimated period of 12-18 months. Clinicians and staff involved in the study will follow the standard operating procedures of the study (SOP): Appendix 3.

1. Clinical Component

PrePex™ devices will be applied and removed by trained operators (nurses/doctors) and participants will be followed up over multiple review visits (Procedures and Schedule) to collect data on the clinical adverse events, pain, and time to complete healing. We will compare the rates of AEs among HIV+ men with PrePex MC to the lower historical proportion of men who experience an AE with surgical MC of 2.0% as seen in Kenya [[22](#_ENREF_22)] and not to the higher rates of AEs of around 3% as seen in both Uganda [[23](#_ENREF_23)] and South Africa [[24](#_ENREF_24)]. Additionally, we will qualitatively compare this data to those collected in Zimbabwe from two previous studies and routine surveillance in Zimbabwe: 1. a comparison group of HIV-uninfected men who were recently circumcised by the same MC providers using the PrePex device; 2. a comparison group of HIV-uninfected men who recently underwent routine VMMC by MC providers using the forceps-guided method.

1. Psychosocial Component

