Individual interviews will be conducted by trained psychosocial interviewers to collect data from HIV-infected participants on satisfaction with the PrePex™ MC procedure, attitudes towards MC, compliance with instructions to refrain from sexual intercourse for 7 weeks post placement [(Day 49 or 6 weeks post removal) or until a clinician tells them that they are fully healed – whichever is later], barriers and motivators to uptake of VMMC through PrePex™, opinions around convenience of the device, tolerance of potential odour and whether participants would recommend PrePex™ MC to others. The interviews with same participants will be held at three points in time: prior to the procedure, two weeks post-procedure, and 90 days post-procedure (Appendices 6-8). In addition all health care providers at facilities where PrePex™ circumcision is offered will be interviewed on the acceptability of the PrePex™ procedure for HIV-infected clients. Interviews with providers (Appendix 9) will take place at one time point approximately 4 weeks post study initiation.

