**Day 21, Day 28, Day 35, Day 42, Day 49, Day 56, Day 63, Day 90**

Patients will be followed in weekly visits until Day49 or until determined fully healed by a clinician (whichever is later). Visits will also occur on Day 90 for those men participating in the psychosocial questionnaire. In each follow-up visit other than Day 90, the following will occur:

- Case Report Forms (CRFs) (Appendix 5) completed by clinician which includes:
  - Clinical exam
  - Evaluation of patient pain level
  - Occurrence of any adverse events
  - Current Medications
  - Photograph of the penis taken if consent granted
  - Reminders to abstain from sexual intercourse until fully healed
  - Assessment of wound healing

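### Abstinence compliance rests on Day 90 recall in up to 103 men, although all 400 already attend weekly visits at which it could be asked

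*Protocol*

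**What the plan says.** Among the secondary objectives, the protocol sets out "To assess compliance with instructions to refrain from sexual intercourse until seven weeks post-placement", or as a clinician instructs, "whichever is later, as a public health safety issue". The risks section gives the reason: male-to-female HIV transmission may be more likely while the wound is healing.

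On who is asked, the overview table in Data Collection reads "1.2.4 (Compliance with instructions) | 103 | Purposive | Interview | QES". The rows for safety, level of care and adverse-event monitoring are instead assigned to the case report form in 400 men. Under Patient interviews the subset is described as "up to 103 men who get circumcised and consent will be randomly selected to have a private" face-to-face interview. On timing, the Psychosocial Component in section B says: "The interviews with same participants will be held at three points in time: prior to the procedure, two weeks post-procedure, and 90 days post-procedure". Table 1 agrees, placing the interviews at D0, D14 and D90.

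For the whole cohort ("The study will involve 400 HIV+ men"), clinical visits run weekly until Day 49 or until the clinician finds the man fully healed, whichever is later. The items listed for the visits from Day 21 onward include an assessment of healing and "Reminders to abstain from sexual intercourse until fully healed". No question on whether intercourse has resumed is listed there or for Day 14.

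**The concern.** The outcome is whether a man had intercourse before the later of Day 49 and clearance. The interview before the procedure cannot inform it. The Day 14 interview covers the first 14 days, seven of them with the device in place. The remaining five weeks to Day 49 rest on one retrospective interview at Day 90, in about a quarter of the cohort.

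Two things are at stake. The first is recall: a man has to remember, weeks later, whether intercourse came before a cut-off, and men cleared after Day 49 also have to place it against their own clearance date. The second is precision: the background section describes data on early resumption in HIV-positive men as scarce, with estimates from 1.1% to 15.7%, and a subset of 103 narrows that range less than the cohort could. The weekly visits that would help with both are already in the schedule.

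**Working it through.** **Inputs from the protocol.** Compliance sample: 103, a ceiling under Patient interviews ("up to 103 men who get circumcised and consent will be randomly selected"). Cohort: 400. Window: Day 0 to Day 49, or later if clearance is later. Interviews after the procedure: Days 14 and 90. Early-resumption rates quoted in the background: 1.1%, 5.5% (10/183) and 15.7% (66/420).

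**The figure of 103.** The protocol gives no rate, precision or confidence level for it, so it cannot be reproduced. The single-proportion formula n = z²p(1−p)/d² lands near 103 under several unstated settings: p = 15.7% with d = 7 points gives 104, and p = 10% with d = 5 points and a finite-population correction for 400 gives 103. None can be attributed to the protocol.

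**Recall.**
- Window closing on Day 49: 90 − 49 = 41 days.
- Cleared on Day 56: 90 − 56 = 34 days. Cleared on Day 63: 90 − 63 = 27 days.
- Share of a 49-day window covered by the Day 14 interview: 14/49 = 29%. Days 15 to 49, which is 35 days, depend on Day 90 alone.
- With weekly asking and full attendance, recall is at most about 7 days.

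**Precision, normal approximation.** The 95% half-width is 1.96·√[p(1−p)/n].
- p = 15.7%, n = 103: 1.96·√(0.157 × 0.843/103) = 7.0 points. With n = 400: 3.6 points.
- p = 5.5%: 4.4 against 2.2 points.
- p = 1.1%: 2.0 against 1.0 points.
- The ratio at any p is √(400/103) = 1.97.

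**Precision, exact (Clopper-Pearson) 95% intervals.**
- About 15.7%: 16/103 gives 9.1-24.0% (width 14.9 points); 63/400 gives 12.3-19.7% (width 7.4 points).
- About 5.5%: 6/103 gives 2.2-12.2%; 22/400 gives 3.5-8.2%.
- About 1.1%: 1/103 has an upper limit of 5.3%; 4/400 has 2.5%.

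**Sensitivity.** If 10% or 20% of the 103 miss Day 90 (my assumption), 93 or 82 men remain and the half-width at 15.7% is 7.4 or 7.9 points. If the 103 are treated as a random sample from a fixed group of 400, it falls to 6.1 points. That version describes these 400 men rather than HIV-positive men in general.

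**Sampling label.** The compliance row calls the sample purposive. Patient interviews says the men are randomly selected, and the other two client-interview rows of the same table say random. These cannot all describe the same 103 men.

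**The case against.** The strongest defence is that a private interview with a trained psychosocial interviewer is a sensible way to ask about a sensitive behaviour. Asking all 400 through the clinicians who give the abstinence reminder reduces variance but not social-desirability bias, and repeated asking may itself change behaviour. The objective is descriptive, with no hypothesis and no precision target, so ±7 points fails no stated requirement; any subset is less precise than the whole. All of this stands. It is why the interviews should be kept, and why the lower precision is a missed opportunity rather than an error.

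Three stronger readings are tempting and are not supported:

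- A reader might infer that the design repeats the weakness the protocol finds in earlier studies. The background calls 15.7% an over-estimate because healing was certified at only a few visits. This trial assesses healing weekly, so it corrects that weakness.
- A reader might infer that the weekly visits record nothing about sexual activity. The visit lists say only what the form includes, and Appendix 5 is not shown. What can be said is that the protocol text lists no such question and the table assigns the objective to the questionnaire.
- A reader might infer that every man's report must be dated against his own healing date. For a man healed by Day 49 the cut-off is fixed. Individual dating matters only for men cleared later, whose recall gap is shorter than 41 days.

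The sampling label should not be overread either. The table also calls the full 400 purposive although all eligible men are to be invited, so loose labelling is the likely explanation. A truly purposive 103 would, however, give no design basis for a confidence interval.

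**Conclusion.** The concern holds as a worthwhile, inexpensive improvement to the design, together with one inconsistency to correct. As the protocol stands, compliance from Day 15 to Day 49 depends on Day 90 recall in up to 103 men. The gap is 41 days for a Day 49 close and 34 or 27 days for clearance on Day 56 or Day 63. Asking all 400 would roughly halve the interval width: 12.3-19.7% instead of 9.1-24.0% at a rate near 15.7%.

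This assumes that the case report form has no item on resumption, that early-resumption rates fall within the range the protocol cites, and that all 400 (or all 103) answer. If Appendix 5 already contains such an item, the table row is what needs correcting. Who is asked, when and with which tool is fixed in this protocol, and no later analysis can recover answers that were not collected.

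**What to change.** Add a short item to the Appendix 5 case report form for all participants, asked before the reminder, at every scheduled visit from Day 14 through the later of Day 49 and clinician clearance: intercourse since the last visit, date of first intercourse, condom used. Asking must not stop at clearance when clearance comes before Day 49, because the window is still open. Define compliance over that same window with n = 400.

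Keep the private Day 14 and Day 90 interviews in the 103 as a group-level check on under-reporting to clinicians. They cannot verify individual answers in the other 297 men. Change the overview-table row to show 400 participants and the case report form, with the questionnaire in the 103 as support, and reconcile the sampling label for the 103 with the random selection under Patient interviews.

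The cost is three short fields at visits that already take place, and a small amendment. The main downside is some under-reporting when a clinician asks. Missed visits after removal, which are chased only by phone or text, will lengthen recall beyond a week for some men.
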